#### Goal assessment

We also aim to understand participants’ goals for implementing their learning from the *Men in Mind* training into practice, and the extent to which these goals are met over the course of the 12-week follow-up period. At T2, the intervention group will therefore be asked to respond to the following open-text item: *Now that you've completed Men in Mind, what are your three main goals for implementing the training into your practice?* Then, at T3, participants’ responses to this item will be presented back to them. They will then be asked to indicate whether they met their goals by responding with *No progress yet; Making progress* or *Achieved*, and to elaborate on why they did or did not meet them via an open-text survey item.

#### Qualitative evaluation

In addition, follow-up qualitative individual semi-structured interviews and focus groups will be completed with approximately 30 participants. These interviews will be transcribed and analyzed using qualitative methods such as thematic analysis [39]. This qualitative component will focus on understanding the acceptability, feasibility and potential efficacy of the training program, in addition to how and when learnings were implemented in practice, and suggestions for future refinement to aid in plans to scale the training program. Example questions will include: *How did you find the training program?; To what extent have you implemented the training in your professional practice?* and *What would you change about the training?*. We will seek to interview an even distribution of intervention and control group participants.

#### Cost analysis

In order to evaluate end-user expenses, as part of the cost analysis, several items will ask participants about their use of additional resources external to the training. For instance, participants will be asked whether, since completing *Men in Mind*, they have engaged with further resources relevant to the training, such as sourcing relevant books, academic articles, podcasts or other resources. If participants indicate ‘yes’, they will be asked to provide details about the specific resource and the approximate cost of access.

### Intervention

*Men in Mind* is an online training program for mental health practitioners working with men [28]. Development, creation, and hosting of the training program was funded by Movember, the world’s largest men’s health charity. The training program was designed for a wide variety of users (i.e., practitioners from mental health fields including psychology and psychiatry, counselling, social work, occupational therapy, mental health/psychiatric nursing, etc.). The goal of the training program is to increase practitioners’ competence and confidence in providing psychotherapy to male clients, by providing targeted training in the implementation of male-oriented adaptations to the process and delivery of psychotherapy. The content development and training program modules are structured around the following domains: (1) men’s gender socialization, masculinities, and gender as a determinant of mental health among men; (2) interactions between male client and practitioner gender socialization and specific considerations for male/female practitioners; (3) engagement and motivation strategies for male clients; (4) understanding and responding to men’s depression and (5) identifying and responding effectively to men’s suicidality. The training format is an interactive, skills-based process in which practitioners are encouraged to reflect on their own gendered experiences, their patterns of interaction with specific male clients, and the particular contexts in which they work. The content is contextualized through four male characters of different ages and backgrounds, who illustrate diverse examples of therapeutic situations over the course of the training program. In addition to text-based content, a suite of 41 professionally-produced, observational “skills-in-action” vignette videos populate the course, in addition to references to current academic and grey literature, practical “toolkit” resources and reflection exercises.

Development of the *Men in Mind* training involved extensive collaboration with learning and user experience design experts, alongside co-refinement of the final content of the intervention with various mental health practitioners and male consumers. These strategies likely contributed to the established acceptability and feasibility of the intervention, demonstrated in the pilot study where the *Men in Mind* training was completed in full by 158 practitioners from 207 initial consent responses (76.3% completion). The allotted 6 weeks for participants to complete the *Men in Mind* training was decided based on the pilot study, where 94% of participants completed the full training program by the conclusion of a 6-week period of access. As the training program is online and self-paced, during the trial, a programmed schedule of reminder emails will be sent to participants to remind them to engage with and complete the training program. These emails will be scheduled based on the stage of the intervention period, and will include personalized messages encouraging engagement with the training program and reminding participants of due dates. All reminder emails will be programmed and sent automatically by Strategic Data (our data management sub-contractor). Given the high rate of completion of the training program in the pilot study, augmenting the training program with the above strategy should be sufficient to enhance adherence.

All participants who are randomized to the intervention group will be given the same *Men in Mind* training, with no modification of the allocated intervention offered. Participants will be invited to complete the training program at their own pace over a 6-week period, and will be free to discontinue training and/or withdraw from the trial at any point. Note that, since no assessments take place during the intervention period, the intervention will only be discontinued at the participants’ volition. Participants will initially work through the modules of the *Men in Mind* training in the order in which they are presented, with no option to skip through the content; however, participants will be able to revisit previously completed content at their discretion until the conclusion of the 6-week intervention period. Post-intervention assessments will be sought from all participants who are randomized, regardless of whether they discontinue training. There are no restrictions on concomitant training in this trial.

### Comparator

Building on the *Men in Mind* single-group pilot study conducted in early 2021, a waitlist-control design was chosen for this trial. This will provide evidence of the efficacy of the *Men in Mind* training; in the pilot it was not possible to attribute observed effects to the intervention because there was no control group.

The trial will compare participants who receive the *Men in Mind* training with those who are waitlisted to receive the training program but who have not yet received it. A waitlist control condition was chosen for two primary reasons. First, all participants will be drawn from a register of practitioners who have previously expressed interest in undertaking the *Men in Mind* training. Therefore, this design will ensure that no participants are denied access to the intervention. An additional benefit, given this sampling, is that this design is likely to reduce dropout from participants who are not interested in completing an alternative, control intervention. Second, the waitlist-control design will capture current practice in the control group as closely as possible, in order to provide an estimate of the benefit of additional training. The SPIRIT diagram below summarizes the protocol for the trial (see Additional file 4: Appendix D for full SPIRIT checklist) (Fig. 1).

**Fig. 1 Fig1:**
[figure not shown]
SPIRIT diagram for the men in mind trial

### Procedure

#### Recruitment

The recruitment target has been set at 380 participants. This number will allow detection of a small-to-medium size effect (Cohen’s *d* = 0.4) with 90% power and alpha 0.05, conservatively assuming a correlation between pre- and post-training scores of 0.5. This sample size allows for up to 30% attrition at T2 (primary endpoint).

Participants will be recruited from a register of practitioners who have voluntarily signed up to receive the training program at https://meninmind.movember.com. The target sample size of 380 participants is considered feasible, given that this register currently contains in excess of 2000 registrations, and the pilot study succeeded in recruiting 67% of those approached. Assuming this rate of consent holds in the trial, a minimum of 567 individuals will be invited to take part (allowing for a non-response rate of 33%). Recruitment will be facilitated by the dissemination of an initial study link via email to a selection of registrants. In addition, the link to the study may be disseminated via social media advertisements and distribution among the personal and professional networks of the investigators, where necessary.

### Consent

Informed consent will be provided online by participants, and required for enrollment in the trial. Participants will be provided with an online plain language statement as part of the initial assessment and asked to indicate their consent by responding to the following survey question: *If you agree with all of the information described here, please indicate your consent to take part by responding below*; presented with *Yes/No* response options. Participants who select *Yes* will be automatically directed to the initial survey assessment; those that select *No* will be directed to close the survey. Participants will be invited to contact the Principal Investigator to discuss any issues or questions that arise during the consenting process.

### Allocation

Participants will be randomized in a 1:1 ratio to either the intervention group (*Men in Mind* training) or control group (6-week waitlist). Permuted block randomization will be performed, using variable sized blocks, with stratification by participant gender (three strata: male, female and non-binary/self-identified gender). The randomization schedule will be generated before recruitment by an investigator unconnected with the day-to-day running of the trial.

Randomization will be programmed by our data management subcontractor, Strategic Data. The allocation schedule will be created by the study statistician and transferred directly to Strategic Data, unseen by the researchers. The eligibility of any individual participant will be automatically assessed and determined prior to group allocation, such that allocation cannot influence the decision to include or exclude the participant.

Online questionnaire data collection will be undertaken by Strategic Data who will use a purpose-built online platform for the survey. They will generate unique URLs for each participant based on their email address, so that participant responses can be connected across all surveys. At the end of trial, Strategic Data will provide the questionnaire data to the researchers in de-identified, blinded format.

### Blinding

Participants will be aware of their group allocation. The research team members, including data analysts, will be blinded to the group allocation of individual participants. The only exception to this is that the Principal Investigator will be unblinded in order to facilitate communication with participants where necessary over the course of the study (e.g., if participants raise questions over the course of the trial regarding technical difficulties etc. this will naturally expose the group to which participants are allocated). All participant data in this study will be self-reported, and the final data set will be completely de-identified, so it is unlikely that any participant contact during the trial will be able to be used to identify participants in the final data set. Observer-rated measures and data analysis will be conducted by blinded members of the research team.

If a participant withdraws from the trial, the Principal Investigator (unblinded) will ensure that participant is not contacted for the next assessment. Participants can contact the researchers via the Principal Investigator’s e-mail address, which is provided on the Plain Language Statement. The Principal Investigator will also seek to determine the reason for the participant’s withdrawal in order to manage the duty of care to participants and troubleshoot any concerns where possible.

### Data collection

The flow diagram above summarizes the data collection procedures in the trial. Initial invitations to take part in the trial will be sent via email. The invitations will contain a brief overview of the study and a link to the plain language statement and consent form as part of the pre-training (T1) survey. Participants will be given a 2-week period (with reminders) within which to provide consent to participate before they are considered a non-responder (Fig. 2).

**Fig. 2 Fig2:**
[figure not shown]
Men in mind trial participant flow diagram

Participants who click through the initial link will be presented with a study plain language statement and consent form. After reading the plain language statement, participants will be asked to indicate their consent by responding to a yes/no survey item. Those who do not consent will be thanked for their time and directed out of the survey. At the end of the 2-week period, should the recruitment target not be met, an additional randomly-selected cohort of individuals from the available register of practitioners who previously expressed interest in completing the *Men in Mind* training will be invited to take part, and also allowed 2 weeks to respond. Consenting participants will then be presented with the full T1 assessment. This will contain self-report measures detailed above, in addition to the objective vignette-based competency assessment. Upon completion of the pre-training assessment, participants will be randomized to either the intervention group or the waitlist control group. Gender entered as part of the T1 survey demographic items will be used as a stratification factor (i.e., male, female and a third stratum encompassing non-binary or self-identified genders) in the randomization process given the significant gender differences in outcomes from our pilot findings.

The intervention group (referred to as “Group A” in participant-facing documentation) will be provided immediate access to the training program for a period of 6 weeks after they complete the T1 assessment. During this time, regular automatic email reminders will be sent to prompt module completion regardless of progress, until participants complete the training program. At the end of the 6-week training period participants will be sent the post-training assessment link (T2) via email. Participants will receive reminders over a 2-week period until the post-training survey is completed. At the conclusion of the 6-week training period, the intervention group will also be informed of the commencement of their follow-up period of 3 months (12 weeks total), and instructed to expect to receive a third and final survey after this period of time. A brief ‘check-in’ style contact will be sent to participants half-way through this follow-up period, as a strategy to minimize attrition and ensure participants’ correct contact details are on-hand. Once the T3 survey is sent, participants will have a 2-week period to complete this with reminders sent until the T3 survey is submitted. Participants who do not complete the T2 survey will still be invited to complete the T3 survey.

After submitting the pre-training survey, the control group (“Group B”) will be informed that their access to the training program will commence after a 6-week period, and following submission of a second survey (T2). During this period, a brief ‘check-in’ style contact will be sent to maintain engagement, equalize contact and, hopefully, minimize attrition and ensure participants’ correct contact details are on hand for all subsequent assessments. Once the T2 survey is sent, participants will receive reminders to complete this over a 2-week period. Access to the training program will be provided automatically on submission of the T2 survey. The control group will be provided access to the training program for a period of 6 weeks, after which their access will be closed off. At the conclusion of their 6 weeks of access a final T3 survey will be sent via email to the control group.

### Data management

All data will be stored indefinitely on secure, password-protected servers in Australia. A unique study identifier will be generated by Strategic Data for each participant and will link responses across time-points. In the first instance, data will only be accessible to members of the research team. However, at the discretion of the Primary Sponsor and Principal Investigator, de-identified data may be shared with researchers who present a methodologically sound proposal and have ethics approval to conduct research using de-identified data obtained in this study.

In addition, the research team will undertake data monitoring over the course of the trial in collaboration with the data collection sub-contractor, Strategic Data, with consultation from the trial statistician. Responses will be inspected to determine data integrity.

### Retention

The strategies designed to enhance adherence to the intervention will also serve to promote participant retention and complete follow-up. The programmed schedule of reminder emails will encourage intervention group participants to continue engaging with the training program. Control group participants will also receive emails, which will remind them of the ‘countdown’ to their intervention access and are designed to keep them engaged throughout the waitlist period. These strategies will likely reduce the frequency of losing participants to follow-up after randomization. Following the protocol applied in the pilot study, once T2/T3 assessments have been sent to participants, they will receive emails at regular intervals encouraging them to complete these assessments. Furthermore, control group participants will only be provided access to the training after they have completed their T2 assessment; this incentive should reduce attrition in this group and maximize the available data for the primary outcome.

### Statistical analysis

Analyses will be undertaken on an intention-to-treat basis and will include all participants in the group to which they were randomized (regardless of actual receipt or uptake of the intervention or withdrawal from the study). Mixed-model repeated measures analyses will be used because of the ability of this approach to include participants with missing data. The model will include factors of study condition (intervention or control group), occasion of measurement (T1, T2 and T3), and their interaction. Analyses will include the effect of the stratification variable, gender, with associated model parameters being retained if they are statistically significant.

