### Primary outcome

The primary outcome will be assessed by a planned comparison of the difference between groups in change of the primary outcome variable (EMITS) from T1 to T2. This test will be undertaken with an alpha of 0.05. An unstructured residual variance–covariance matrix will accommodate within-participant dependency. Tests of significance will use appropriate degrees of freedom adjustment where necessary (e.g., the Kenward-Roger method based on the observed information matrix). Where necessary, transformation of the outcome variable will be undertaken to ensure distributional assumptions of the model are met.

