### Future directions and conclusions

Findings from this trial will inform the future refinement and potential dissemination of the *Men in Mind* training. In particular, examining any subgroup differences in change on outcome measures following exposure to the intervention, alongside qualitative insights gleaned from interviews and/or focus groups with participants, will shed light on potential avenues to specifically target the scaled rollout of the *Men in Mind* training among populations of practitioners who may benefit most. For example, practitioners working in youth-specific mental health services may find areas of the training program that are particularly beneficial, especially in light of high service discontinuation rates among young men [12, 43]. In addition, the *Men in Mind* pilot evaluation revealed an interaction between change on the EMITS and practitioner gender, where female participants began with significantly lower self-reported skill with male clients relative to male practitioners. Whilst the trial will incorporate stratification based on practitioner gender to account for these effects, the in-built qualitative evaluation will shed light on further ways in which female practitioners might benefit from the training program.

To conclude, there undoubtedly exist a number of structural and organizational barriers to help-seeking that are known to affect men’s uptake of mental health services [5, 6]. Yet establishing the efficacy of the Men in Mind training will aid the field by illuminating practitioner training as a viable avenue to ensuring the increasing numbers of help-seeking men are met with services that meet their needs.

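### Gender, the stratification factor, stays in the primary model only if its unnamed terms are statistically significant, so the trial's own data choose that model

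*Protocol article*

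**What the plan says.** The base model is fixed in the Statistical analysis section of the protocol article: "The model will include factors of study condition (intervention or control group), occasion of measurement (T1, T2 and T3), and their interaction". The next sentence adds gender conditionally: "Analyses will include the effect of the stratification variable, gender, with associated model parameters being retained if they are statistically significant". It does not say which parameters are meant (main effect, gender x occasion, gender x condition x occasion), and it gives no threshold.

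The Primary outcome section under Statistical analysis defines one test, a "planned comparison of the difference between groups in change of the primary outcome variable (EMITS) from T1 to T2", and adds: "This test will be undertaken with an alpha of 0.05". It does not say how the contrast is averaged over gender if a gender interaction is in the model.

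The Allocation section describes permuted blocks "with stratification by participant gender (three strata: male, female and non-binary/self-identified gender". The Data collection section gives the reason for stratifying: "given the significant gender differences in outcomes from our pilot findings". The Background reports that the pilot found a significant interaction between practitioner gender and pre-post change. Future directions and conclusions returns to this: "Whilst the trial will incorporate stratification based on practitioner gender to account for these effects".

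Two other places bear on the question. The section on demographic information lists gender among variables collected partly for post hoc subgroup work. The Subgroup analyses section says such analyses are exploratory and reported apart from the primary outcome. Neither overrides the retention rule.

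**The concern.** The investigators judged gender important enough, before the trial, to stratify on it. A factor used to constrain the randomisation belongs in the model whatever its p-value in the trial. Under the written rule, a preliminary test on the outcome data decides which primary model is fitted. Because secondary outcomes follow the same methods, different outcomes could end up with different gender terms.

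Which term is kept matters. T1 is a response in this model, so a gender difference that is constant over time essentially cancels out of T1-T2 change. Gender x occasion can adjust that change for gender, but it does not alter what the treatment contrast estimates. Gender x condition x occasion can. Once it is in the model there is one treatment effect per gender, and a single planned contrast has a meaning only after weights over the three strata are chosen.

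The statement in Future directions also needs care. Stratified allocation balances gender between arms, including the baseline difference seen in the pilot. It does not by itself deal with a training effect that differs by gender.

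**Working it through.** **Planned size reproduced.** Inputs from Recruitment: d = 0.4, power 90%, alpha 0.05 (taken as two-sided), pre-post correlation 0.5, attrition 30%.
- SD of change = sqrt(2(1 - 0.5)) = 1 in SD units.
- n per arm = 2(1.960 + 1.282)^2 / 0.4^2 = 131.3, so 132 per arm and 264 in total.
- 264 / 0.70 = 377.1, so 378 with equal arms, against the stated 380.
- 380 x 0.70 = 266 completers, 133 per arm. SE = sqrt(2/133) = 0.123, power 90.4%.

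**Case A: only gender or gender x occasion is kept or dropped.** If gender explains a share R² of the variance of change, leaving it out inflates the SE by 1/sqrt(1 - R²) - 1.
- R² = 5%: 1/sqrt(0.95) - 1 = 2.6%. A 2-df F test on 266 completers (noncentrality 266 x 0.05/0.95 = 14.0) keeps the term in 92.5% of trials, so the average inflation is 0.075 x 2.6% = 0.2%.
- R² = 2%: inflation 1.0%, term kept in 53% of trials, average about 0.5%.
- R² = 1%: inflation 0.5%, term kept in 29%, average about 0.4%.

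In simulation with no treatment effect and a female shift of 0.3 SD in change, type I error was 0.047-0.048 with gender always left out and 0.050 with gender always in. Any error from dropping gender is slight and conservative.

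**Case B: gender x condition x occasion is a candidate and is kept.** The article gives neither the gender mix nor effects by gender, so both are assumptions. Mixes used: 75/23/2% and 60/37/3% (female/male/third stratum).

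With equal weights of one third per stratum, the SE relative to share weighting is sqrt((1/9) x sum of 1/p):
- 75/23/2: sqrt((1.333 + 4.348 + 50)/9) = 2.49
- 60/37/3: sqrt((1.667 + 2.703 + 33.333)/9) = 2.05

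The third stratum supplies nearly all of this.

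Simulation of the rule on T1-T2 change scores: 266 completers, terms kept at p < 0.05, 20,000-40,000 runs per scenario, not the full three-occasion model.

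| Scenario | Interaction kept | Equal weights or male reference | Observed-share weights |
|---|---|---|---|
| No effect (type I error) | about 5% | 0.062-0.067 | 0.049-0.050 |
| Common d = 0.4 (power) | about 5% | 0.88 | 0.90 |
| Female effect larger by 0.3-0.5 SD, average 0.4 (power) | 14-41% | 0.54-0.79 | 0.90 |

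In the last scenario, when the interaction was kept, the mean contrast was 0.07-0.24 with equal weights and -0.18 to 0.02 at the male reference level. With observed-share weights it stayed at 0.40.

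**Check of the remedy.** With gender always in the model and no gender-by-treatment term, type I error was 0.049-0.050, power was 0.89-0.90 and the mean estimate was 0.40, at the same sample size.

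**The case against.** The strongest reply is that the article never names a gender x condition x occasion term. It lists condition, occasion and their interaction, then the effect of gender. It places subgroup effects in post hoc, exploratory work apart from the primary outcome. On that reading the rule concerns only gender terms without treatment, and Case A shows that this hardly matters. How marginal means are weighted is also a detail normally left to an analysis plan, which is not shown. The pilot had no control group, so it showed gender x time, not gender x treatment.

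Most of this stands. It disposes of a stronger reading that a reader might infer, namely that the sentence as written costs the trial a large part of its power. That conclusion needs three things the article does not state: the three-way term as a candidate, equal or reference-level weighting, and particular gender shares and effect sizes. With observed-share weights the loss disappears.

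The reply leaves two things untouched. The retention rule is stated in the article itself, so it is not merely a detail left to another document. And the plural, unnamed parameters leave the three-way term open, with a pilot finding that makes a gender interaction foreseeable.

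**Conclusion.** The point holds as a fault of specification and should be fixed. A significance test on the trial's data selects the primary model for a factor that was fixed by design, and the candidate terms are not named. No loss of power has been demonstrated.

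- If only gender or gender x occasion is affected, the SE rises by at most 2.6% for a gender effect explaining 5% of variance, and by about 0.5% or less on average over the values tried.
- If the three-way term were retained, the T1-T2 contrast would rest on an unstated weighting. The type I error of 0.062-0.067 and the power of 0.54-0.88 are a worst case under equal or reference-level weights. They depend on assumed gender shares and, below 0.88, on assumed differences in effect by gender.
- With observed-share weights, type I error and power stay at their planned values.

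Confidence is high that the rule makes the model data-dependent. It is low for any particular worst-case figure.

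**What to change.** Replace the retention sentence in Statistical analysis with wording such as:

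> Gender (three strata) and gender x occasion are fixed terms in all models regardless of significance. The primary T1-T2 contrast comes from the model without gender x condition terms. Gender x condition x occasion is examined in a separate moderation analysis, and any average over gender uses observed stratum proportions.

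The change should be made before any analysis by group, so that the choice of model cannot be linked to the result. It is wording only. It uses 2 degrees of freedom for gender and 2 x 2 = 4 for gender x occasion, 6 in all, and leaves the target of 380 unchanged.
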